## **128 Impact of LAIV on the nasopharyngeal microbiome**

Initial sequence data analysis will be performed as described above. Univariate and multivariate linear regression models will be used to study the effect of vaccination with LAIV on microbiota profiles at day 7 and 21 post-vaccination, adjusting for factors such as antibiotic use within the last 1 month, age and nutritional status in all multivariate analyses. Relative effect sizes and their 95% confidence intervals will be calculated for all significant OTUs. Inter-individual variability between vaccinated and unvaccinated children at day 7 and 21 will be calculated using Pearson correlations and tested for significance using the Mann-Whitney U test.

The relative and absolute abundance of the OTUs representing *S. pneumoniae* and *S. aureus* will be compared at day 7 and 21 following vaccination with baseline data and validated via qPCR. Differences in *S. pneumoniae* and *S. aureus* density at day 7 and 21 post-LAIV will be estimated using a regression model, including a fixed effect for the vaccine group and random effects for other relevant factors.

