### **Model selection by backwards selection for generalised linear and logistic mixed-effects models**

A multivariable model was first constructed using pneumococcal density (continuous data) as the response variable and including all possible covariates of interest: Group (ref: control vs LAIV), Study timepoint (ref: D0 vs D7 and D21), year of recruitment (ref:2017 vs 2018), presence of asymptomatic respiratory viruses at baseline, age in months, sex, presence of a smoker in the household, type of cooking (re:outdoor open fire vs indoor kitchen). Interactions between group and study timepoint, group and year of recruitment, as well as group and the presence of asymptomatic respiratory viruses were also included.

Backward selection was then undertaken, removing covariates to construct a new model and comparing this reduced model with the previous model using ANOVA-derived P values and Akaike information criteria (AIC). Non-informative covariates were sequentially removed in this way to arrive at the most parsimonious model for our data. Non-significant interaction terms were first removed prior to single covariates. The final model is as stated below:

Pneumococcal density ~ study timepoint + group\*year of recruitment + presence of baseline respiratory viruses + age in months + type of cooking + (1 | participant ID)

A logistic mixed-effects model with pneumococcal carriage (categorical data) as the response variable and including covariates of interest was constructed in a similar way, for each group (LAIV or control) individually. The final model is as stated below:

Presence of pneumococcal carriage ~ study timepoint + presence of baseline respiratory viruses + age in months + type of cooking + (1 | participant ID)

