## 13 Aims and Objectives

### 14 Study objectives

#### 15 Primary

- (i) To identify novel early systemic and mucosal molecular signatures following LAIV that are associated with subsequent robust nasal and oral influenza-specific immunoglobulin A (IgA) responses, in order to provide insight into the mechanisms of successful mucosal immunization.
- (ii) To identify associations between nasopharyngeal microbiota and nasal and oral influenza-specific IgA responses post-LAIV in Gambian children, to explore whether microbiome variability can explain suboptimal immune responses in some individuals to live intranasal mucosal vaccines in Sub-Saharan Africa.
- (iii) To establish whether LAIV impacts the nasopharyngeal microbiome, with a specific focus on the burden of *S. pneumoniae*.

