### **72 Medical and drug history**

A medical history will be obtained by the investigator, sub-investigator or study nurse. Any abnormal findings requiring further treatment will be managed according to local practice or an appropriate referral made according to the nature of the condition. A lack of exclusion criteria will be confirmed.

All concomitant medications a child is receiving will be recorded in the CRF. Data on antibiotic use within the last month will also be collected and recorded. The use of concomitant medication, other than those considered exclusion criteria, does not preclude recruitment (see section 5.3.2).

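### Recent antibiotic use and nutritional status, which the protocol names as adjustment factors and collects, were left out of the pneumococcal density models without a stated reason

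*Combined protocol and SAP*

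**What the plan says.** Section 128 plans regression models for the effect of LAIV on day-7 and day-21 microbiota profiles, "adjusting for factors such as antibiotic use within the last 1 month, age and nutritional status in all multivariate analyses". A later paragraph of that section gives pneumococcal and staphylococcal density its own model: a "regression model, including a fixed effect for the vaccine group and random effects for other relevant factors". Those other factors are not named.

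The section serves the third primary objective: "To establish whether LAIV impacts the nasopharyngeal microbiome, with a specific focus on the burden of" *S. pneumoniae* (section 15). Section 129 adds that relevant covariates will be taken into account in all analyses. It also gives nutritional status and recent antibiotic use as examples of baseline characteristics to compare between groups, vaccinated versus unvaccinated children among them.

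Both variables were to be collected. Section 72 says: "Data on antibiotic use within the last month will also be collected and recorded". Section 73 requires height and weight at each visit and a Z-score.

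The appendix text on model selection describes the starting density model as "including all possible covariates of interest: Group (ref: control vs LAIV), Study timepoint (ref: D0 vs D7 and D21), year of recruitment", followed by "presence of asymptomatic respiratory viruses at baseline, age in months, sex, presence of a smoker in the household, type of cooking", with interactions of group with timepoint, year and baseline virus. The final density model keeps timepoint, group by year, baseline virus, age and cooking. For carriage, the appendix says only that a similar procedure was used within each group, and gives the final terms.

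**The concern.** Backward selection cannot keep a term that was never offered to it. If two of the three factors that the protocol names were not candidates, the density estimates are unadjusted for them whatever the data would have shown.

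The two kinds of contrast in these models are affected differently. LAIV versus control is randomised, so the omission costs some precision and leaves any chance imbalance uncorrected. Baseline virus positivity is not randomised. A child treated for an illness in the month before entry could differ both in virus detection and in pneumococcal density, so residual confounding is possible.

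Other rules do not close the gap. Section 58 removes children given unplanned antibiotics after starting the study from the microbiome analyses, but not those treated before entry. Section 55 excludes fever or acute respiratory infection in the previous 14 days but not antibiotic use, so a child treated 15 to 30 days earlier is eligible. It excludes a weight-for-height Z-score below -3, so milder undernutrition remains.

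**Working it through.** **Planned factors against the model.**

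- Age: named in section 128; in the candidate list; in the final density model.
- Antibiotics in the past month: named in sections 128 and 129; collected under section 72; not a candidate; not in Tables S2 to S6, S8 or S9.
- Nutritional status: named in sections 128 and 129; collected under section 73; not a candidate; not in those tables.

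So one of three named factors was offered to the density model. For carriage no candidate list is printed. The omission there is inferred from the similar procedure, the final terms and Table S1.

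**Size for the randomised contrast.** The documents give no antibiotic rates or effects, so these are assumptions: 15% of children exposed, and a density reduction of 0.3 to 0.5 log10.

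- Arm sizes 213 and 108 (Table S10). SD of the chance difference in exposure = sqrt(0.15 × 0.85 × (1/213 + 1/108)) = 0.042.
- Shift at one SD: 0.042 × 0.3 = 0.013 to 0.042 × 0.5 = 0.021 log10.
- Because Table S2 has a group-by-year term, its LAIV coefficient is the 2017 contrast. With the 2017 targets in section 51 (65 per group, so 130 versus 65), the SD is sqrt(0.15 × 0.85 × (1/130 + 1/65)) = 0.054, and the shift at 0.5 log10 is 0.027.

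The distance of the LAIV results from the 5% threshold is the yardstick:

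- Table S2: +0.339, SE 0.129; 0.339 − 1.96 × 0.129 = 0.086.
- Table S4: +0.323, SE 0.127, 168 df; t = 2.54, p = 0.012 as reported; distance 0.072.

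A 1.96-SD imbalance, with exposure of 5% to 30% and effects of 0.25 to 1.0 log10 (assumed), shifts the coefficient by 0.01 to 0.11 at 213 versus 108, and by 0.02 to 0.14 at 130 versus 65. With an effect of 0.5 log10 the largest shift is 0.068, at 30% exposure and the 2017 sizes, which is below both distances. Crossing the threshold takes a larger effect together with an unfavourable imbalance. The final model has no group-by-timepoint term, so a baseline imbalance enters the LAIV coefficient directly and is not differenced out.

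**Size for baseline virus.** Table S2 gives +0.259, SE 0.097. Assume recent antibiotic use is 10 to 20 points higher in virus-positive children and lowers density by 0.3 to 0.5 log10. Then:

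- Bias = 0.10 × (−0.3) = −0.03 to 0.20 × (−0.5) = −0.10.
- Adjusted estimate: 0.259 + 0.03 = 0.289 to 0.259 + 0.10 = 0.359.
- Relative size: 0.03/0.259 = 12% to 0.10/0.259 = 39%; the upper end is about one SE.

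The bias is towards zero, so adjustment would strengthen the reported association.

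**Nutritional status.** The documents give neither its spread nor its effect on density, so no figure is offered.

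**The case against.** The strongest reply is about scope. The clause naming the factors belongs to a sentence on microbiota profiles, and density has a separate sentence with unnamed factors. The phrase *such as* also makes the list illustrative. This reply stands in part: section 128 does not plainly bind the density model to these two covariates. It does not dispose of the point. The density model sits under the same heading and serves the same objective, section 129 extends relevant covariates to all analyses, and the protocol itself treats these two as relevant. The appendix presents its list as exhaustive and does not say why they were dropped.

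A reader might infer that the plan was breached in all eight regression tables (S1 to S6, S8 and S9). The documents do not support that. S1, S3 and S6 are control-group analyses, and S8 and S9 compare high with low vaccine-virus shedding. None contains the LAIV-versus-control contrast that section 128 describes. Relating shedding to pneumococcal density is not a protocol objective either: exploratory objective (iii) in section 16 relates shedding to immune responses.

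It can also be said that the 14-day exclusion weakens the link between recent illness, antibiotics and an asymptomatic virus at entry. That is fair. It makes the assumed 10 to 20 point difference uncertain, but does not rule out earlier treatment. The baseline comparison planned in section 129 is not shown in this document, so whether antibiotic use was rare or balanced cannot be judged from it.

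**Conclusion.** The point holds for the density models: two collected factors that the protocol names were not candidates, and no reason is given. For carriage it is an inference.

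The expected consequence for the LAIV result is small, about 0.02 log10 at 15% exposure and a 0.5 log10 effect, or 16% of the Table S2 standard error (0.021/0.129). The loss of precision cannot be quantified from the documents. A reader might infer that the LAIV finding is confounded or would not survive adjustment. Randomisation rules out systematic confounding of that contrast, and only the upper end of the assumed range would cross the 5% threshold.

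For baseline virus, residual confounding is possible, but under the stated assumptions it makes +0.259 an underestimate. The opposite inference, that the virus association is inflated, does not follow from them.

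For shedding, no mechanism linking earlier antibiotics to vaccine-virus shedding is given, so confounding cannot be asserted. Table S8 is nevertheless near the threshold (0.380 − 1.96 × 0.167 = 0.053), which justifies a check.

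**What to change.** Refit the density models with a LAIV term (Tables S2, S4 and S5) with two covariates forced in and exempt from backward selection: antibiotic use in the month before day 0 (yes/no), and a day-0 nutritional measure such as weight-for-height Z-score. Show these estimates beside the current ones. If covariate values are missing, also refit the current model on the same children, so that any change reflects adjustment and not a different sample.

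As a secondary check, do the same for Tables S8 and S9, stating that these were not protocol-planned analyses. If the two factors stay out of the main model, give the reason and label the omission a departure from the plan. State the candidate list for the carriage model as well.

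The cost is a re-run with two variables that the protocol already required, a few degrees of freedom, and the loss of any children with missing covariate values.

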## 20 Study design

### 21 Type of study and design

All primary objectives and most exploratory objectives will be addressed through the conduct of a phase 4, randomized, controlled clinical vaccine trial. A total of 330 healthy children aged 24 – 59 months will be enrolled into one of three groups of equal size (3 x 110 children):

- (i) LAIV-vaccinated (Group A - blood sample at day 0, 2, 21)
- (ii) LAIV-vaccinated (Group B - blood sample at day 0, 7, 21)
- (iii) Control group (Group C)

Allocation concealment will be maintained from the start through the use of sealed envelopes. Block randomization stratified by sex will be used and a randomization sequence will be generated by an MRC Statistician not involved in the study. Investigators will not be blinded to group allocation from this point onwards as the sampling schedule differs between groups. Local laboratory staff will therefore not be blinded for this reason, but samples sent to external laboratories will be blinded (see section 3.2.3).

Two LAIV-vaccinated groups are included in order to achieve several exploratory objectives, which require blood sampling at different time points following vaccination, whilst minimizing the number of times children are bled times (i.e. 2nd blood sample at either day 3 or day 7 post-LAIV, but not both). The unvaccinated subjects will serve as a control group for the primary objective of assessing the impact of LAIV on the nasopharyngeal microbiome. Section 8 details the statistical considerations made to decide on the sample sizes to be recruited. The vaccination and sampling schedules for groups A, B and C are detailed in Tables 1.

Group C subjects will be administered LAIV after the NPS is taken on their day 21 visit, to offer them the same level of protection against influenza illness by participating in the study as those in groups A, B and D.

An additional 35 healthy children aged 24 – 59 months will be recruited in the 2nd phase of recruitment (Jan – June 2018) to assess the objective of how modulation of the nasopharyngeal microbiome with antibiotics impacts the mucosal immunogenicity to LAIV

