**Figure 1. Sample size estimates to detect 2-fold gene expression changes**

## 122 Identifying associations between nasopharyngeal microbiota and nasal and oral influenza-specific IgA responses post-LAIV in Gambian children, to explore whether microbiome variability can explain suboptimal immune responses in some individuals

Calculations were performed using the Shiny application for determining sample size calculations for case-control microbiome studies (<https://fedematt.shinyapps.io/shinyMB/>) [73]. Simulations were run using the anterior nares-derived microbiome data available on the application, estimating that analyses would consider the most abundant 150 operational taxonomic units (OTUs). IgA responders and non-responders were defined as cases and controls respectively and sample size/power calculations performed to detect a 1.5-fold

difference in abundance in the 10 most abundant OTUs and 2-fold difference in abundance in the next 10 most abundant OTUs, between the two groups (Figure 2).

Power calculations were performed using these parameters, for a range of sample sizes from 50 – 150 per group and using the Wilcoxon-Mann-Whitney (WMW) test applied to each OTU individually and the resulting *P*-values multiplicity adjusted with the Benjamini and Hochberg method to control the false discovery rate ('WMWavg' – Figure 3). Prior data suggest that approximately 50% of children receiving LAIV are IgA responders, using a definition of  $\geq 2$ -fold rise in IgA from baseline [7]. At an alpha of 0.05, 82 subjects per group would give a power of 80%. A sample size of  $n = 100$  per group was selected (i.e.  $n = 200$  children given LAIV, accounting for approximately 50% showing an IgA response), which even accounting for some drop outs would give a power of  $\geq 80\%$ .

If required, the complexity of data may be reduced by defining microbiota composition according to 8 distinct profiles described by the [name] group [1] rather than variability across 20 different OTUs/species, thus reducing the need for correction for multiple testing and increasing the power significantly.

[figure not shown]

**Figure 2. Simulations of anterior nares derived microbiome data showing differences between cases and controls of the 20 most abundant OTUs.**

[figure not shown]

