**Figure 3. Sample size and power estimates to detect differences in the top 20 most abundant OTUs between two groups (1.5-fold difference in the top 10 abundant OTUs and 2-fold difference in the next 10 most abundant OTUs). WMWavg refers to the Wilcoxon-Mann-Whitney test as applied to each OTU and multiplicity adjusted to control for false discovery rate.**

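### At OTU level, effect sizes and confidence intervals are promised for significant OTUs and for no others, with significance left undefined

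*Combined protocol and SAP*

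**What the plan says.** Primary objective (iii), in section 15, is "To establish whether LAIV impacts the nasopharyngeal microbiome, with a specific focus on the burden of" *S. pneumoniae*. Section 18 lists microbiome profiles at baseline, day 7 and day 21 as a primary endpoint, separately from *S. pneumoniae* density.

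Section 128 (Impact of LAIV on the nasopharyngeal microbiome) plans univariate and multivariate linear regression of microbiota profiles on vaccination at days 7 and 21. For the output it says: "Relative effect sizes and their 95% confidence intervals will be calculated for all significant OTUs". It does not define significance and names no multiplicity adjustment.

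For two species, *S. pneumoniae* and *S. aureus*, the same section is unconditional. Of the difference between groups it says: "density at day 7 and 21 post-LAIV will be estimated using a regression model, including a fixed effect for the vaccine group". The relative and absolute abundance of the OTUs representing these species is also to be compared with baseline, again without a significance condition.

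Multiplicity is addressed elsewhere, but for another comparison. In section 122, for IgA responders against non-responders, P values are "multiplicity adjusted with the Benjamini and Hochberg method to control the false discovery rate". Section 127 plans adjustment for multiple comparisons, again for IgA responders against non-responders.

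**The concern.** The sentence makes the reporting of an OTU's estimate depend on that OTU's own test. This has two consequences.

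- An estimate passes the filter more easily when chance has pushed it away from zero, so the reported set overstates the true effects on average.
- An OTU that fails the filter gets no interval. A reader cannot tell whether LAIV leaves that taxon unchanged or the trial was too imprecise to say.

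The second consequence matters here because excluding a meaningful shift after LAIV would itself answer part of objective (iii). The undefined threshold adds to the difficulty. With two kinds of model and two visits, an OTU could be called significant in one analysis and not in another, and the plan does not say which one decides.

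**Working it through.** **Is there a plan figure to start from?** Not for this comparison. The nearest is in section 122: "At an alpha of 0.05, 82 subjects per group would give a power of 80" per cent, for a "1.5-fold difference in the top 10 abundant OTUs and 2-fold difference in the next 10 most abundant OTUs". It compares IgA responders with non-responders and comes from a simulation tool whose dispersion is not in the documents, so it cannot be reproduced independently. Working backwards with a two-sample normal approximation on the ln scale, the SD that makes 82 per group give 80% power at an unadjusted two-sided 0.05 is ln(fold) / (2.802 × √(2/82)). That is 0.93 for a 1.5-fold and 1.58 for a 2-fold difference. Section 123 covers power for *S. pneumoniae* density only. OTU-level power for LAIV against control is therefore an assumption in what follows.

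**Step 1: inflation given selection.** Let δ be the true effect divided by its standard error, c the critical value, and z ~ N(δ, 1).

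- Power = Φ(δ − c) + Φ(−c − δ)
- Mean of |z| given |z| > c = [δΦ(δ − c) + φ(c − δ) − δΦ(−c − δ) + φ(c + δ)] / power
- Inflation = that mean / δ

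Take 80% power at 0.05, so c = 1.960 and δ = 2.802. The lower-tail terms are negligible. Then (2.802 × 0.800 + 0.280) / 0.800 = 3.15, and 3.15 / 2.802 = 1.12.

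Now keep the same OTU and sample size (δ = 2.802) and tighten the threshold to 0.005, so c = 2.807. Power falls to 0.498. Then (2.802 × 0.498 + 0.399) / 0.498 = 3.60, and 3.60 / 2.802 = 1.29.

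| Assumed power at 0.05 | δ | Inflation at 0.05 | Power at 0.005, same δ | Inflation at 0.005, same δ |
|---|---|---|---|---|
| 80% | 2.80 | 1.12 | 50% | 1.29 |
| 50% | 1.96 | 1.41 | 20% | 1.72 |
| 30% | 1.43 | 1.81 | 8.5% | 2.28 |

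The inflation falls to 1.03 at 95% power and rises to 3.7 at 10% power (threshold 0.05).

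**Step 2: the same effect under a Benjamini-Hochberg rule.** Inputs:

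- 150 OTUs, with 10 at 1.5-fold, 10 at 2-fold and 130 null. The counts and effect sizes are borrowed from section 122.
- Three groups of 110 (section 21), so 220 LAIV against 110 control. After the roughly 10% attrition in section 51, 198 and 99 remain, rounded to 200 and 100.
- FDR 5%. This rule is an assumption, because section 128 states none.
- ln-scale SD assumed from 0.9 to 2.0, with independent normal estimates and 3,000 runs.

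| Assumed SD | True 1.5-fold: power; mean if reported | True 2-fold: power; mean if reported | Coverage of reported unadjusted 95% CIs | OTUs with an interval, of 150 |
|---|---|---|---|---|
| 0.9 | 83%; 1.55 | about 100%; 2.00 | 91.4% | 19 |
| 1.5 | 25%; 1.90 | 81%; 2.13 | 90.5% | 11 |
| 2.0 | 8%; 2.37 | 38%; 2.55 | 83.9% | 5 |

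Means are geometric means of the absolute effect. The direction is the same throughout. The size runs from negligible to large across a plausible range of SD.

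**Step 3: with the filter removed.** If every tested OTU is tabulated, there is no selection on significance. Under the same normal model the expected ratio of estimate to truth is 1.00 and coverage is 95%.

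**The case against.** The strongest answer is that the objective's stated focus escapes the problem. The *S. pneumoniae* and *S. aureus* density differences are to be estimated whatever their P value. The appendix shows density results handled that way: Table S5 gives the LAIV effect in 2018 as −0.139 with standard error 0.155 and P = 0.37. From that a reader can form −0.139 ± 1.96 × 0.155, or about −0.44 to +0.17 log10 copies/µl. This stands. A reader might infer that all reported LAIV effects on the microbiome will be exaggerated, or that objective (iii) can yield only inflated positives and uninformative nulls. The documents do not support either inference. It remains true that section 128 names no interval for the density estimates.

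Second, the sentence commits to intervals for significant OTUs and does not forbid them for others. That is correct: it is a gap in the commitment and not a rule of suppression. But nothing elsewhere in the plan fills the gap.

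Third, the power levels are hypothetical. That also stands, so the factors above are illustrations and not estimates for this trial.

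Finally, a reader might expect FDR control to shrink the inflation. Holding power fixed at 80%, 50% and 30% does give 1.10, 1.28 and 1.51 at a 0.005 threshold. But that comparison silently enlarges the true effect by 1.30, 1.43 and 1.59 times. For the same OTU and the same children, the stricter threshold raises the inflation.

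**Conclusion.** The concern holds as a reporting gap confined to the OTU-level results. Followed as written, section 128 yields OTU estimates selected on significance, hence biased away from zero, and leaves non-significant OTUs without any measure of precision. It does so with an undefined threshold and no multiplicity rule of its own.

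The direction of the bias is certain. Its size is not, because the documents give neither power nor dispersion for OTUs in the LAIV-versus-control comparison. It is slight for OTUs with 80% power or more at an unadjusted 0.05 threshold (12% or less) and substantial at 50% or below (a factor of 1.4 or more). The figures assume approximately normal estimates, two-sided tests, and a test and interval taken from the same model. The two density analyses, the sample size and the conduct of the trial are untouched.

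**What to change.** Replace the sentence in section 128 with a commitment to report the LAIV-versus-control effect size and 95% CI at day 7 and at day 21 for every OTU tested. Define the tested set in advance as all OTUs above a stated abundance cut-off. Give FDR-adjusted P values alongside, define significance on the adjusted P value, and name the model that supplies it. In the same edit, name the 95% CI for the *S. pneumoniae* and *S. aureus* density differences.

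The models have to be fitted to every OTU in order to learn which are significant, so the cost is a longer supplementary table.

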### **50 Selection and withdrawal of participants**

#### **51 Selection of participants**

The study will randomize 330 children between 24 and 59 months, followed by sequential recruitment of a further 35 children within the same age range (see section 3.1), which allows for approximately 10% participant attrition during the study and required sample sizes to achieve primary objectives (Section 8). Screening of potentially eligible children will continue until this number or the recruitment end date (30.06.2018) is reached. Recruitment will take place over two six month periods, January – June 2017 and January – June 2018 (first subject first visit, FSFV to last subject first visit, LSFV of each season). These months have been chosen to coincide with periods when wild-type influenza infections are likely to be at their lowest, therefore least likelihood of interference with study endpoints. The recruitment target for season 1 (January – June 2017) will be 195 children (65:65:65 into groups A, B and C) and season 2 (January – June 2018) 170 children (45:45:45 into groups A, B and C, followed by 35 into group D – see section 3.1). This represents 29 – 33 children per month or approximately 7 - 8 children per week. Any shortfall in numbers caused by lack of recruitment or withdrawal in season 1 will be made up in season 2 by increasing target numbers.

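### The test of between-child microbiome variability leaves its unit of analysis open; if all within-arm pairs enter, about 70-85% of null comparisons would come out significant

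*Combined protocol and SAP*

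**What the plan says.** Protocol section 128, on the impact of LAIV on the microbiome, names the quantity to be tested as "Inter-individual variability between vaccinated and unvaccinated children at day 7 and 21". As to method, it says that this quantity "will be calculated using Pearson correlations and tested for significance using the Mann-Whitney U test". That sentence is the whole specification. It does not say whether the correlations are all pairs within each arm, within-arm against between-arm pairs, or one summary per child. It gives no alpha for this test and names no permutation procedure or adjustment for shared children. Section 129 adds only a general undertaking to check model assumptions.

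On the design, children are "enrolled into one of three groups of equal size (3 x 110 children"), and groups A and B both receive LAIV on day 0. On the role of group C, the protocol says: "The unvaccinated subjects will serve as a control group for the primary objective of assessing the impact of LAIV on the nasopharyngeal microbiome". The recruitment target allows for "approximately 10% participant attrition during the study". The primary endpoints include microbiome profiles and *S. pneumoniae* density. Inter-individual variability is not itself a listed endpoint.

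**The concern.** A correlation that describes variation *between* children needs two children, so each value most naturally belongs to a pair. Every child then contributes to many values. A child with an unusual profile lowers all of its correlations together, so those values are not separate pieces of evidence. Mann-Whitney counts each as an independent observation and takes its precision from the number of pairs, not the number of children.

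The plan could therefore report that LAIV changes how much children differ from one another when it has no effect. The comparison bears on a primary objective and is made at two visits.

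**Working it through.** The plan gives no error rate, power or sample size for this test, so there is no figure of its own to reproduce.

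**Inputs.**
- Arms: 220 LAIV (A and B pooled, an assumption; group D left out) against 110 controls. With 10% attrition, 198 against 99. A 1:1 comparison, 110 against 110, was also run.
- Alpha: two-sided 0.05, assumed. The plan uses 0.05 only in sample-size work for other analyses (for example "At an alpha of 0.05, 82 subjects per group would give a power of 80"%).
- Profile length: 150 OTUs, borrowed from the sample-size section for the IgA objective ("estimating that analyses would consider the most abundant 150 operational taxonomic units (OTUs"), with 20 also tried.
- Abundance structure: not given beyond a mention of "8 distinct profiles described by the" a collaborating group, so it was assumed and varied.

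**Number of pairs**, n(n−1)/2. LAIV: 198 × 197 / 2 = 19,503. Control: 99 × 98 / 2 = 4,851. Each LAIV child sits in 197 pairs and each control child in 98.

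**Analytic check, all within-arm pairs.** Let ρ be the correlation between two pairs that share one child. Each pair shares a child with 2(n−2) others, so the variance of an arm's pair mean is inflated by 1 + 2(n−2)ρ. Treating the test as a comparison of means, with ρ = 0.15:
- LAIV: 1 + 2 × 196 × 0.15 = 59.8
- Control: 1 + 2 × 97 × 0.15 = 30.1
- Overall inflation: (59.8/19,503 + 30.1/4,851) / (1/19,503 + 1/4,851) = 36.0
- Type I error: 2 × [1 − Φ(1.96/√36.0)] = 74%

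The same formula gives 28% at ρ = 0.01, 58% at 0.05, 69% at 0.10 and 82% at 0.30. In the seven main simulation models ρ was 0.13-0.28.

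**Null simulation.** Both arms were drawn from the same distribution. The seven models were Dirichlet at two dispersions, lognormal at SD 1 and 2, log-scale abundances, and eight unequal profiles with 150 or 20 OTUs. Each used 300 replicates, so the Monte Carlo SE near 75% is √(0.75 × 0.25/300) = 2.5 points. Five further eight-profile variants were run at 198 against 99 for the first row only. Rejection rates at nominal 5%:

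| Values entering the test | 2:1 arms (220 vs 110; 198 vs 99) | 1:1 arms (110 vs 110) |
|---|---|---|
| All within-LAIV vs all within-control pairs | 70-84% | 70-78% |
| Pooled within-arm vs between-arm pairs | 49-68% | 0.3-4% |
| Within-LAIV vs between-arm pairs | 65-79% | 54-64% |
| One mean within-arm correlation per child | 29-38% | 30-36% |
| Arm labels permuted between whole children | 3.3-6.7% | 4.7-7.3% |

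Further null simulations at 198 against 99 gave about 3-6% for each child's correlation with the pooled mean profile. A Dirichlet run gave 4.0-6.3% for correlation with the child's own arm's mean profile and 4.2-5.3% for disjoint pairs.

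**Why per-child means still fail.** Write a pair's correlation as a constant plus an effect for each child, a_i + a_j, plus noise. A child's mean correlation is then roughly a_i plus the arm's average effect, so the arm mean contains that average twice. Its true variance is about 4 times what the spread between children suggests, giving 2 × [1 − Φ(1.96/√4)] = 2 × [1 − Φ(0.98)] = 33%. This agrees with the simulated 29-38%.

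**The case against.** The strongest reply is that the plan does not say that all pairs enter. A reader might infer that the test as written has a false-positive rate of 70-80%, or that it will usually declare an effect where none exists. The documents do not support that. They fix neither the unit nor an alpha for this test, and they do not give the abundance distribution. Some readings that are still between-child hold near 5%, and pooled within-arm against between-arm pairs at 1:1 is conservative. This part of the reply stands, and the size must be stated as conditional.

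It does not rescue the plan. The valid readings require the analyst to choose a reference profile or disjoint pairs, and the text mentions neither. With the natural 2:1 comparison, every pairwise reading examined that lets children recur fails badly, as does the per-child mean. The general promise to check assumptions supplies no remedy, because the dependence is built into the statistic. A child's own baseline-to-follow-up correlation would be an independent value, but it measures change within a child, which is not what the sentence describes.

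The second reply is scope, and it also stands. A reader might infer that primary objective (iii) as a whole is undermined. It is not: the regression of profiles on vaccination, the OTU comparisons and the *S. pneumoniae* density model do not use this test, and the sample size for the objective rests on density.

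Children given unplanned antibiotics are excluded from these microbiome analyses, so the real counts would be somewhat lower. That changes the rate little.

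**Conclusion.** The concern holds in conditional form. Section 128 applies Mann-Whitney to between-child correlations without stating the unit or allowing for shared children. The error rate depends on that unstated choice:
- roughly 70-85% if all within-arm pairs enter;
- about 30-38% with one mean within-arm correlation per child;
- near 5% only for readings such as correlation with a common mean profile or disjoint pairs.

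These figures assume two-sided 0.05, groups A and B pooled (1:1 was also checked), about 10% attrition and the abundance models listed. They are not figures from the documents. The analytic check shows that the conclusion does not depend on strong dependence: at 198 against 99, ρ = 0.01 already gives 28%. The defect is limited to one supporting comparison, made at two visits, and should be corrected before that comparison is run.

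**What to change.** State in section 128 that the child is the unit of analysis. Pearson correlations can stay. At each visit, compute the mean within-arm correlation in each arm and take the difference as the statistic. Obtain its p-value by permuting arm labels between whole children, within sex and recruitment year. This follows the design: randomization is stratified by sex, and the planned allocation is equal across A, B and C in each season (65:65:65, then 45:45:45). Also state which groups form the vaccinated arm, the abundance scale and the alpha.

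The simulations permuted children without strata, because none were modelled, and used the mean-rank difference of within-arm pairs as the statistic. Label permutation tests the null that LAIV leaves the distribution of profiles unchanged, and the text should say so.

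A permutation dispersion test on a distance matrix is an acceptable alternative. The protocol mentions UniFrac clustering only for baseline data, so day 7 and day 21 matrices would have to be computed from the OTU tables.

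The cost is a few sentences of text and a little more computation, with no new data. The downside is fewer nominally significant results.
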